### Monitoring of participants’ compliance, medications used during the trial, adverse effect and blinding

2.9

Researchers involved in administering each intervention sessions will constantly comply with a logbook completion to monitor participant compliance (i.e., adherence to each intervention sessions, complaints related to the treatments methods). In case of any change in the patient’s clinical timetable researcher involved in the intervention sessions will promptly inform the study principal investigators (FP, LC, and LT) to check the treatment plan together with the clinical setting demands. Psychotropic medications with serotonergic activity will not be permitted during the study, general medications (such as antibiotics, anti-inflammatory drugs, and vitamin supplements) will be allowed and recorded in the logbook for each patient. Adverse event, i.e., any unfavorable and unintended sign or symptom associated with the intervention, will be monitored and recorded during the trial and addressed adequately. To this purpose a checklist based on Brunoni et al. (41) will be filled in by all participants during the first session of each stimulation arm. Mitigation of adverse events will involve the use of a fade-in period prior reaching the maximum intensity of stimulation to reduce discomfort and the use of conductive gel to reduce skin irritation or burns. Blinding will be assessed via administering two *ad-hoc* scales, a Patients’ Informed, and an Assessors’ Informed Post-Intervention Scale, in which patients and investigators will be asked to guess the order of real and sham stimulation and to rate their confidence on a 5-point Likert scale.

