### Intervention

2.4

The intervention will consist of multifocal brain stimulation combined with cognitive training. In a cross-over design, 16 stimulation sessions (two sessions for week; freely scheduled from Monday to Friday on participants’ and institutional needs) will be delivered in two blocks (8 real and 8 sham stimulation sessions) for 10 weeks. The first and the last stimulation sessions of each block (namely sessions 1, 8, 9 and 16; Figure 1) will be preceded and followed by 5-min resting state EEG recordings with eyes-opened. Recruited participants will be randomly assigned to a “SHAM-REAL” stimulation group (G1) or a “REAL-SHAM” stimulation group (G2; Figure 1) by computer-generated random numbers; one investigator (FP) will manage generation of allocation sequence and participants’ assignment to the groups. The experimenters responsible for delivering the stimulation (LC) will be blind to the stimulation being delivered during each session. Throughout the study, all participants will undergo traditional cognitive stimulation therapy, embracing within each session paper-and-pencil and computerized activities during a face-to-face interaction with the therapist at the rehabilitation service. Activities will target memory, attention, and executive functions (24, 25); the level of difficulty will be tailored on the patients’ neuropsychological profile and progressively adjusted based on patients’ response to the treatment. Each session of cognitive training will last 40 min and will follow the brain stimulation session.

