### Hybrid EEG and HD-tDCS montage

2.6

A hybrid device will be employed to record EEG and deliver anodal tDCS (StarStim 32, Neuroelectrics, Spain); the stimulation/EEG sessions will be managed by the NIC2 software v2.0.11 (Neuroelectrics, Spain).

The configuration will include 8 electrodes positioned in a non-conductive neoprene cap. Direct current will be delivered using small, round gel electrodes (Ag/AgCl, 3.14 cm2), each filled with conductive electrolyte gel and positioned according to the international 10/10 EEG system. Anodal direct current delivered will be set at a total intensity of 2 mA equally distributed to the stimulation electrodes placed over F3 and T7 (1 mA each). Six return electrodes will be placed around the anodal electrodes over Fp1, FC1, F7, C3, CP5 and P7 (Figure 2) and the overall return current (−2 mA) will be equally distributed among these electrodes. This distribution of electrical current makes the minimal cathodal effects induced at the return positions not able to lead relevant changes in brain activity (Figure 2). Each stimulation session (real and sham) will last 21 min, including 30s fade-in and 30s fade-off periods. In the sham stimulation, the montage will be identical to that of the real stimulation, but the real anodal stimulation will be delivered for a duration of 30 s only. This montage will reproduce the same itching sensation associated with real stimulation thus allowing effective blinding (34).

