### Sample size justification and statistics

2.8

The final sample size of 60 participants is estimated based on a sample size calculation on G*Power (v. 3.1.9.7) suggesting a sample size of at least 48 participants to compare the two groups along three-time points with an effect size = 0.25, power = 0.80, *ε* = 0.75, and a Bonferroni-adjusted *α* = 0.0125 (0.05/4 primary cognitive outcomes see below) and considering a dropout rate up to 30% from previous studies (37, 38).

Demographic data will be reported using descriptive statistics. Primary outcomes will be the measures of cognitive (MOCA, FAB, FCSRT, Stoop scores) and affective (GDS scores) functioning, while independence in daily living (ADL and IADL scores) and EEG parameters will be considered as secondary outcomes. Intention-To-Treat (ITT) analyses (39), which includes all randomized participants in the groups assigned, regardless of their adherence with the entry criteria, will be adopted. ITT analysis admits noncompliance and protocol deviations and gives an unbiased estimate of the intervention effect. Missing data will be dealt with by using a mixed-effect model approach which accommodates missing data under the missing-at-random assumption (40). To assess the effect of the intervention on multiple dependent variables simultaneously, repeated-measures analyses of variance (ANOVAs) will be conducted on the primary outcomes and secondary outcomes separately with the factors Group (G1 vs. G2) and Time (T1-T3). Moreover, multiple regression models will be used to identify the factors associated with the treatment outcome, considering gender, age, education, CRS scores, and EEG power spectrum at baseline as predictors and post intervention measures of general cognitive functioning (MOCA and FAB) and functional independence measures as criteria.

To assess possible sequence or carryover effects, an exploratory comparison of treatment effects between the two randomization arms (sham first over real vs. real first over sham) will be performed.

Statistical analysis will be performed using IBM® SPSS® Advanced Statistics and R package (R Foundation). Statistical significance will be set at *p* < 0.05.

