### Withdrawal criteria

2.11

Study participants will receive explicit information about the possibility to withdraw from the study at any point. Participants will be withdrawn if they suffer from any intolerable adverse effects resulting from tDCS or if they fail to attend required site visits, or they are noncompliant with or reluctant towards the study procedures. For transparency, though, data from all participants withdrawn from the study will be included in the final report. Unblinding will be possible only in case of withdrawal from the study.

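### Section 2.9 limits adverse events to those associated with the intervention, so events put down to age or disease may go unrecorded in both the real and sham blocks

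*Protocol article*

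**What the plan says.** Section 2.9 of the protocol article contains a definition and two recording routes.

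- **Definition:** "Adverse event, i.e., any unfavorable and unintended sign or symptom associated with the intervention, will be monitored and recorded during the trial".
- **Checklist:** a published tDCS checklist, introduced as serving this purpose, "will be filled in by all participants during the first session of each stimulation arm".
- **Logbook:** the researchers who run the sessions keep a "logbook completion to monitor participant compliance (i.e., adherence to each intervention sessions, complaints related to the treatments methods"). General medications are entered there too.

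Three other places bear on the point.

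- Section 2.4: the sessions "will be delivered in two blocks (8 real and 8 sham stimulation sessions) for 10 weeks", and the staff who deliver stimulation "will be blind to the stimulation being delivered during each session".
- Section 2.6, on the sham: "This montage will reproduce the same itching sensation associated with real stimulation thus allowing effective blinding".
- Section 2.11, on leaving the study: "Participants will be withdrawn if they suffer from any intolerable adverse effects resulting from tDCS".

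Section 2.8, on statistics, lists no adverse-event outcome and no real-versus-sham safety comparison.

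**The concern.** The definition makes a link to the intervention a condition for being an adverse event at all. If that link is understood as cause, someone has to form a view on cause before the event qualifies, and an event thought unrelated does not qualify.

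Participants are 55 to 85 years old, have MCI or mild dementia, and are treated over about 10 weeks. Falls, fainting, confusion and admissions are plausible in such a group and easily put down to age or disease.

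The sham block is the trial's own control for such background events. Whether stimulation adds to them is best judged by comparing all events under real and sham stimulation. Sorting events by presumed cause before recording discards part of that information, and a harm that nobody expects is the one most likely to be sorted out. Two centres will also apply the phrase, and each could draw the line in a different place.

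**Working it through.** The documents state no adverse-event rate or count, so there is no figure to reproduce. The check has two parts: a reading of the text, and an illustration with assumed rates.

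**1. Which reading of the definition is more natural?**

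- The defining sentence already has a time limit (the trial period). A purely temporal link to the intervention would add little to it.
- The logbook takes complaints that concern the treatment methods, which is also a test of relatedness.
- Against this, the sentence does not say that the event must be caused by the intervention, and it describes no causality step.

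The causal reading is favoured but not certain.

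**2. Is there a route that needs no judgement of relatedness?**

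- Checklist: completed by all participants in the first session of each of 2 arms. Sessions in total: 8 + 8 = 16. Coverage: 2/16 = 12.5%.
- Remaining 14 sessions and the time between visits: the stated routes are the definition and the complaints entry in the logbook. Both carry a relatedness qualifier.

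On the causal reading, an event in the middle of a block that is put down to age or disease therefore has no clear stated place to be recorded.

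**3. What would filtering do to a real-sham comparison?**

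Assumptions, none from the documents: true event rates of 0.30 (real) and 0.20 (sham), and a probability *s* that an event is recorded. From section 2.8: 60 participants, each treated under both conditions.

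Recorded rate = true rate × *s*. Expected count = 60 × recorded rate. RR is the ratio and RD the difference of the recorded rates.

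| *s* real / *s* sham | Count real | Count sham | RR | RD |
|---|---|---|---|---|
| 1 / 1 | 60 × 0.30 = 18 | 60 × 0.20 = 12 | 1.5 | 0.10 |
| 0.8 / 0.8 | 60 × 0.24 = 14.4 | 60 × 0.16 = 9.6 | 1.5 | 0.08 |
| 0.5 / 0.5 | 60 × 0.15 = 9 | 60 × 0.10 = 6 | 1.5 | 0.05 |
| 0.8 / 0.5 | 60 × 0.24 = 14.4 | 60 × 0.10 = 6 | 2.4 | 0.14 |

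With true rates of 0.40 and 0.20 the pattern is the same. An equal 50% loss takes 24 versus 12 to 12 versus 6, with RR 2.0 unchanged and RD falling from 0.20 to 0.10.

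Equal filtering thus lowers counts and shrinks the absolute difference but leaves the ratio alone. The ratio moves only when recording differs by block: in the last row of the table it is 1.5 × (0.8/0.5) = 2.4.

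**4. What if the filter removes only events that really are unrelated?**

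Add a background rate *b* to both blocks: RD = (0.30 + *b*) − (0.20 + *b*) = 0.10 for any *b*. RR is 1.4 at *b* = 0.05 (0.35/0.25) and 1.33 at *b* = 0.10 (0.40/0.30).

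A perfectly accurate filter would therefore do no harm to the absolute difference. The difference is understated when some stimulation-caused events are wrongly judged unrelated, which is the risk with unexpected harms.

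**The case against.** The strongest reply is that this is one loosely worded clause in a condensed article, that the link to the intervention may be meant in time only, and that relatedness ratings and logbook fields usually sit in the full protocol. The first part stands as far as it goes: the phrase is ambiguous. The condensation argument excuses what is left out, whereas here a definition is printed and is too narrow on its more natural reading.

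Three stronger claims that a reader might infer are not supported.

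- **That blinded operators must judge cause before logging an event.** No section gives them that task, and the one named instrument is filled in by participants in the same way under real and sham.
- **That the real-sham comparison will be biased.** Operators are blind and the sham is meant to reproduce the itching. A filter applied blind is expected to act equally in both blocks and to preserve the ratio. Bias would need recording that differs by block. The plan sets out to assess blinding, and nothing in it shows that blinding fails.
- **That the withdrawal rule in section 2.11 applies the same filter.** Its wording is openly causal, but it governs leaving the study, not recording. The same section also says that data from withdrawn participants will be in the final report.

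Two further points limit the concern. Depressive symptoms, cognition and daily functioning are measured at T1, T2 and T3 without any test of relatedness, so worsening there is partly captured. And section 2.8 plans no safety comparison, so no stated analysis is damaged; what suffers is the safety record from which any such comparison would be made.

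**Conclusion.** The point holds in a limited form. The definition in section 2.9, read causally, leaves out events thought unrelated, and the only unfiltered instrument covers 2 of 16 sessions. Total events may be under-recorded and the absolute real-sham difference understated.

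This rests on the causal reading, and, for the understated difference, on some stimulation-caused events being judged unrelated. The size cannot be derived from the documents; the figures above only show the direction under assumed rates. It is a cheap improvement to safety recording and does not call the efficacy analysis into question.

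**What to change.** In section 2.9:

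- Define an adverse event as any untoward sign or symptom from session 1 to T3, whether or not it is thought related to the intervention.
- Enter each one in the existing logbook with date and session.
- Rate relatedness in a separate field, while the rater is still blind to the order of real and sham.
- Report all events, and related events, by real and sham block.

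The withdrawal rule in section 2.11 stays as it is.

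The cost is one sentence in the protocol and one logbook column, with no extra visits or staff. The downside is more entries of trivial or unrelated events.

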### Human ethics, consent to participate and compensation

2.10

Ethics approval has been obtained for this study from “Comitato Etico Territoriale Campania 1” (protocol n. 409, 29–11-23, n. 9/2023) and from the Institutional Ethic Committee of the Department of Psychology, University of Campania “Luigi Vanvitelli” (approval n. 30/2024). All participants enrolled in the study are required to provide a signed informed consent document; all family members and family doctors of the patients will be informed about study participation from their relative/assisted patient. No compensation is provided to patients participating to the study. All procedures will follow the ethical standards set by the Declaration of Helsinki.

### Withdrawal criteria

2.11

Study participants will receive explicit information about the possibility to withdraw from the study at any point. Participants will be withdrawn if they suffer from any intolerable adverse effects resulting from tDCS or if they fail to attend required site visits, or they are noncompliant with or reluctant towards the study procedures. For transparency, though, data from all participants withdrawn from the study will be included in the final report. Unblinding will be possible only in case of withdrawal from the study.

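### The plan promises intention-to-treat with a mixed model but names a repeated-measures ANOVA as the test, and its withdrawal rule removes the non-compliers that policy says it admits

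*Protocol article*

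**What the plan says.** Section 2.8 (Sample size justification and statistics) makes three statements about the same outcome data.

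- The analysis set is ITT, "which includes all randomized participants in the groups assigned, regardless of their adherence with the entry criteria". The section adds: "ITT analysis admits noncompliance and protocol deviations and gives an unbiased estimate of the intervention effect".
- On missing data: "Missing data will be dealt with by using a mixed-effect model approach which accommodates missing data under the missing-at-random assumption".
- On the test: "repeated-measures analyses of variance (ANOVAs) will be conducted on the primary outcomes and secondary outcomes separately", with factors Group (G1, G2) and Time (T1 to T3). Nothing says how this relates to the mixed model in the sentence before.

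The sample size in the same section comes from a G*Power calculation for two groups at three time points, with a nonsphericity value ε = 0.75.

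Section 2.11 (Withdrawal criteria) says participants will be withdrawn for intolerable adverse effects, or if "they fail to attend required site visits, or they are noncompliant with or reluctant towards the study procedures". It adds that "data from all participants withdrawn from the study will be included in the final report". It does not say whether T2 and T3 are still collected after withdrawal, or how the data enter the efficacy analysis.

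Section 2.2 (Participants) ends data collection once at least 60 participants have completed the whole intervention. The Abstract instead speaks of 60 patients being enrolled.

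**The concern.** There are two separate conflicts.

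The first is the model. A conventional repeated-measures ANOVA needs a full row of T1, T2 and T3 and deletes anyone with a gap, including the visits that person did attend. A mixed model uses every observed visit. When visits are missing the two do not analyse the same people, and the article fixes both without saying which gives the primary result.

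The second is the withdrawal rule. ITT is meant to keep non-compliers in the comparison as randomised. Section 2.11 speaks of withdrawal from the study, not of stopping stimulation, and its grounds include non-compliance, reluctance and missed visits. If outcome assessment ends with withdrawal, the rule itself adds missing T2 and T3 scores, for reasons related to tolerance and adherence. That strains the missing-at-random assumption and the description of the estimate as unbiased.

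At stake is whether the result reported as ITT is in practice an analysis of compliant completers. In a crossover, someone lost during the first period provides no within-person comparison of real and sham, and selective loss can shift the contrast between sequences.

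**Working it through.** **1. The plan's own sample size.** Inputs from Section 2.8: f = 0.25, α = 0.05/4 = 0.0125, ε = 0.75, k = 2 groups, m = 3 time points, target power 0.80. The article gives no correlation between repeated measures, so ρ = 0.5 is assumed. For the Group × Time interaction:

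- λ = f²·N·m·ε/(1 − ρ)
- df1 = (k − 1)(m − 1)ε = 1 × 2 × 0.75 = 1.5
- df2 = (N − k)(m − 1)ε

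At N = 48, λ = 0.0625 × 48 × 3 × 0.75/0.5 = 13.5 and df2 = 46 × 2 × 0.75 = 69, giving power 0.816. At N = 46 power is 0.794. The stated minimum of 48 is reproduced, as an interaction test in a conventional repeated-measures ANOVA. The required N depends strongly on ρ: 66 at ρ = 0.3 and 30 at ρ = 0.7.

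**2. If 60 is the number randomised.** The Abstract says this, and it fits the Discussion's plan to recruit 25–30% above the minimum (48 × 1.25 = 60). At the 30% dropout in Section 2.8, 0.30 × 60 = 18 are lost and 42 have all three visits. At N = 42, λ = 0.0625 × 42 × 3 × 0.75/0.5 = 11.81 and df2 = 40 × 2 × 0.75 = 60.

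| ρ (assumed) | Power, 60 complete | Power, 42 complete |
|---|---|---|
| 0.3 | 0.77 | 0.56 |
| 0.5 | 0.91 | 0.745 |
| 0.7 | 0.99 | 0.95 |

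At ρ = 0.5, 25% dropout leaves 45 complete cases (power 0.783) and 20% leaves 48 (0.816). Keeping 48 complete cases at 30% dropout needs 48/0.7 = 68.6, so 69 randomised.

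**3. If 60 is the number of completers (Section 2.2).** Power at ρ = 0.5 is 0.910 even on complete cases. At 30% dropout, 60/0.7 = 85.7, so about 86 are randomised and 86 − 60 = 26 are left out of a complete-case analysis. The problem is then departure from ITT rather than power.

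**4. Can deletion bias the comparison?** An illustration on assumed values: 60 randomised, no true effect, ρ = 0.5, T3 missing in about 30%, 4,000 simulated trials. In one group low T2 scorers were more likely to leave; in the other, leaving was random. The group difference in T2 − T1 change averaged 0.17 SD when anyone without T3 was deleted, and 0.00 SD when all observed T1 and T2 scores were used. With completely random dropout in both groups, both averaged 0.00. Deletion can therefore produce a spurious difference when loss is selective; the size and direction in this trial are unknown.

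**5. The withdrawal rule.** No arithmetic applies. Section 2.8 says non-compliance is admitted; Section 2.11 makes it a ground for leaving the study. Both can hold only if outcomes are still collected after withdrawal and enter the analysis, and the article states neither.

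**The case against.** The strongest reply is that Section 2.8 should be read as a whole. It commits to all randomised participants and to a mixed model, no sentence restricts the analysis to completers, and deleting incomplete cases is a property of a conventional method that the article never mentions. The ANOVA sentence could simply name the Group × Time effects to be tested from the mixed model. That reading is possible, and it is why the documents do not show that ITT is abandoned. It does not settle the matter: the article names a different method without linking the two, and sizing the trial with ε points to the conventional ANOVA.

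Several stronger readings are tempting and are not supported.

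- A reader might infer that T2 and T3 are never collected after withdrawal. The article does not say so, and a condensed article may leave that detail to the full protocol. What stands is the conflict between the two sections, which a promise to report withdrawn participants' data does not resolve.
- A reader might infer that the investigators create all the missing data, for reasons of cognitive state. The grounds mention adverse effects, attendance, compliance and reluctance, not cognition. People who miss visits or decline procedures would often be missing anyway.
- A reader might take the fall in power from 0.91 to 0.745 as the price of using ANOVA. It requires 60 to be the number randomised and ρ = 0.5. Most of it is plain loss of data, which a mixed model would recover only in part.
- A reader might see a bias in "Unblinding will be possible only in case of withdrawal from the study". That sentence is a restriction. If withdrawn participants are not assessed again, unblinding them cannot affect an outcome; it matters only if assessment continues.

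**Conclusion.** The point holds as a contradiction to be resolved. Section 2.8 fixes two methods that treat incomplete participants differently, and Section 2.11 withdraws people for behaviour that Section 2.8 says the analysis admits. Following the named test and the withdrawal rule can give a completer analysis labelled ITT; the text does not establish that it will.

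The size depends on which section governs the number 60. With 60 randomised and 30% dropout, a complete-case analysis has 42 participants and power of about 0.75. With 60 completers, power is kept and about 26 of 86 randomised are left out. The power figure rests on an assumed correlation and on deletion of incomplete cases. The stated minimum of 48 is not in dispute. The change should be made, since it is specific and cheap.

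**What to change.** 1. In Section 2.8, replace the repeated-measures ANOVA with one primary mixed model containing Group, Time and their interaction, using all available visits of every randomised participant.
2. In Section 2.11, separate stopping sessions from leaving the study: neither stopping sessions nor non-compliance ends outcome assessment, and T2 and T3 are still sought by blinded assessors unless consent is withdrawn. State how withdrawn participants' data enter the efficacy analysis. The clinical grounds for ending stimulation stay as they are.
3. Reconcile Sections 2.2, 2.8 and 2.11, saying whether 60 counts randomised participants or completers.

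The cost is protocol wording, plus already-scheduled test visits for participants who stop sessions. A mixed model gains little from someone with only T1, so the second change matters as much as the first.
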